#### Sample size

The Cochrane systematic review [3] found only one small trial directly comparing the effectiveness of a chemical treatment, salicylic acid, with cryotherapy in patients with warts on their feet alone [4]. This poor quality study found a 58% cure rate among the patients allocated to cryotherapy compared with 41% among those treated with salicylic acid. This difference of 17% was not statistically significant. The overall cure rates from this study are smaller than those observed in two placebo controlled trials of salicylic acid, both of which reported cure rates of 85% for active treatment, possibly because more resistant verrucae were included in the study comparing cryotherapy with salicylic acid. The EVERT trial is powered to show a 15% difference in effectiveness. Sufficient patients will be recruited to give 80% power (5% two sided significance) to show a difference in cure rates of 70% versus 85% at 12 weeks. This requires 120 patients in each group; after allowing for a 10% drop-out rate, 133 will be required in each treatment group (i.e. 266 in total).

### Statistical analysis

Data on baseline demographics such as gender, age, type and duration of verrucae, and previous treatments will be summarised and descriptive summary statistics provided. For variables with continuous measures we will report the mean and standard deviation. For categorical data we will report numbers and percent.

Analysis will be by 'intention to treat'. All patients will be included in their initially randomised groups whether or not they received their allocated treatment. Analyses will be conducted blind to group. There will be a single primary analysis at the end of the study using 5% two sided significance tests. The primary outcome is complete clearance of all verrucae at 12 weeks. The two treatment groups will be compared using simple proportions of cure or not cured using the Chi squared test.

For the secondary outcomes stricter statistical levels of significance will be adopted (i.e. p = 0.01) to reduce the chance of type I error. Survival analysis of patient self-reported time to clearance of verrucae, censoring for loss to follow up, will be tested for using Cox regression adjusting for relevant co-variates to be defined before the analysis. The recurrence/clearance of verrucae at 6 months will be analysed in the same way as the primary outcome measure. The primary analysis will be repeated, but controlling for age, whether or not the verruca has been previously treated and type of verruca. Should numbers be sufficient, in order to examine whether mosaic verrucae respond less well to treatment than simple verrucae, the primary analysis will be repeated, but the type of verruca mosaic/simple will be included as a covariate and also an interaction term verruca type*treatment will be included [5]. As patients and healthcare professionals are not blinded to treatment, we will carry out a second, sub group analysis, assessing the influence of participant's treatment preference on treatment outcomes and the results of the cost-effectiveness analysis.

Data on side effects and pain intensity during and after treatment, use of painkillers, reasons for seeking treatment for the verruca, treatment details, patient satisfaction with treatment and number of verrucae, will be summarised and descriptive summary statistics provided. The number of patients discontinuing treatment prematurely for any reason will be summarised by treatment group and by reasons for discontinuation. The incidence of all suspected adverse treatment reactions will be summarised by treatment group.

For each outcome measure, the number of non-responders (missing data) will be calculated for each treatment group. We shall compare at each follow-up point the number and proportion of non-responders in each group and the type of non-responder e.g. proportion of males not responding in each group. Appropriate methods for dealing with missing data will be employed and sensitivity analyses performed.

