## Methods

### Design

This is an open, pragmatic, two-arm, multicentre, randomised controlled trial. Patients with verrucae are randomised equally to cryotherapy using liquid nitrogen delivered by a healthcare professional (a podiatrist, practice nurse or GP) or once daily self-treatment with 50% salicylic acid paste (Verrugon; William Ransom & Son Plc, Hitchin, UK). Two hundred and sixty-six patients are being enrolled into the study at recruiting sites in the UK and Southern Ireland for a period of 24 weeks, with treatment lasting a maximum of 8 or 9 weeks. The primary outcome is assessed at 12 weeks. Recruitment started in October 2006 and will continue until approximately December 2009. The study has been approved by the Trent Multi-centre Research Ethics Committee (Reference Number 04/mre04/59), the Medicines and Healthcare Products Regulatory Agency (MHRA), The Irish Medicines Board (IMB) and the ethics or National Health Service (NHS) research and development committee responsible for each site. The study is being conducted in accordance with the ethical principles in the Declaration of Helsinki and good practice guidelines on the proper conduct of research.

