### Participants

Patients are eligible if they (i) have a verruca that in the opinion of the healthcare professional is suitable for treatment with both salicylic acid and cryotherapy and (ii) are aged 12 years and over. Patients are excluded if they (i) are currently in a trial evaluating other treatments for their verruca, (ii) have impaired healing e.g. due to diabetes, peripheral vascular disease or any other condition which means the patient has impaired healing, (iii) are immunosuppressed e.g. have agammaglobulinaemia, or are currently taking immunosuppressant drugs such as oral corticosteroids, (iv) are unable to give informed consent, (v) are currently on renal dialysis, (vi) have cold intolerance e.g. Raynaud's syndrome or cold urticaria, or (vii) have any of the following conditions: blood dyscrasias of unknown origin, cryoglobulinaemia, cryofibrinogenaemia, collagen and auto-immune disease.

Recruitment is taking place in both podiatry outpatient clinics (hospital-based or university podiatry school-based) and general practice at eight recruiting sites in the UK and one in Southern Ireland. To aid recruitment, a number of strategies have been adopted to increase the number of patients presenting to the clinics and GP practices e.g. the trial has been advertised at pharmacies, GP surgery waiting rooms, swimming pools, libraries and secondary schools local to the recruiting sites.

All patients, and their parent/guardian for patients under the age of 16 years, are given written information about the study and opportunity to discuss the study with the trial coordinator and/or site investigator prior to their decision whether to take part. Written informed consent is obtained from the patient, or the parent/guardian for those under 16 years, prior to being randomised. The healthcare professional at the recruiting site randomises the patient using the remote, independent York Trials Unit (University of York, UK) telephone or web-based randomisation service. Randomisation is simple, that is it is not restricted in any way, for example by stratification or blocked allocation. The allocation sequence is computer generated, with the treatment allocation being concealed from both the healthcare professional and York Trials Unit until the moment of randomisation.

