### Study evaluations

#### Primary outcome

The primary outcome is complete clearance of all verrucae at 12 weeks as observed on digital photographs taken by the healthcare professional delivering the treatment at baseline and 12 weeks and assessed by an independent healthcare professional. Blinded healthcare professional assessment of clearance is also performed at the 12 week appointment, to be used if for some reason the digital photograph is not interpretable. Clearance of verrucae is defined as the restoration of normal skin upon close inspection, as assessed by the healthcare professional. Participants who do not attend their 12 week outcome assessment appointment are asked if they are willing to take a digital photograph of their foot.

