#### Further data collected

Other data collected in the questionnaires completed by the patients include pain associated with the verrucae (on a 5 point scale, from 'not at all' to 'extremely'), number of days over a two week period the patient has self-treated with salicylic acid, reasons for seeking treatment for the verruca(e), how long the patient has had the verruca(e), whether they received previous treatment for the verruca(e), willingness to receive the same treatment again if they had another verruca, if the patient had to stop treatment, reasons for this and whether they started another treatment, number of previous verrucae and age at which they occurred. Treatment details for both groups, number and type of verrucae and participant's treatment preference are collected via a questionnaire completed by the healthcare professional. Data on adverse events, self-reported by the patient (verbally and/or by questionnaire) or elicited by the healthcare professional following questioning of the patient at each study visit, are collected.

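### The primary chi-squared test is valid and adequately powered, but neither it nor the planned adjusted repeat uses number of verrucae, so cheap extra precision is forgone

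*Protocol article*

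**What the plan says.** All references are to the protocol article.

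- **Allocation (Participants):** "Randomisation is simple, that is it is not restricted in any way, for example by stratification or blocked allocation". The Design section gives equal allocation.
- **Endpoint (Primary outcome):** "The primary outcome is complete clearance of all verrucae at 12 weeks". It is one yes/no result per patient, whatever the number of lesions.
- **Primary test (Statistical analysis):** "The two treatment groups will be compared using simple proportions of cure or not cured using the Chi squared test", at two-sided 5%.
- **Adjusted analysis (Statistical analysis):** "The primary analysis will be repeated, but controlling for age, whether or not the verruca has been previously treated and type of verruca". If numbers allow, a further model adds a type-by-treatment interaction.
- **Number of verrucae (Further data collected):** "number and type of verrucae and participant's treatment preference are collected via a questionnaire completed by the healthcare professional". The Statistical analysis section plans only a descriptive summary of number.
- **Cox model for time to clearance:** its covariates are left to be defined before the analysis, so number could enter there. The covariates of the 12-week adjusted repeat are named, and number is not among them.

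**The concern.** A patient with several verrucae counts as cured only if all of them go. Unless lesions in one patient clear or persist together, the chance of success falls as their number rises. Number is therefore tied to the outcome by the endpoint's definition. The design does not balance it, the primary test does not use it, and the adjusted repeat leaves it out although it is recorded.

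Two things are at stake. One is extra power in a trial planned at 80%. The other is an estimate that takes account of any chance difference between the arms in number of verrucae.

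**Working it through.** **1. The plan's own sample size.** Inputs from the Sample size section: 70% versus 85%, two-sided 5%, 80% power, 10% drop-out. With the pooled-variance formula and mean rate 0.775:

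n = [1.96·√(2·0.775·0.225) + 0.8416·√(0.70·0.30 + 0.85·0.15)]² / 0.15² = [1.157 + 0.489]² / 0.0225 ≈ 120.5, so 121 per arm.

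The article states 120, at which power is 79.8%. Then 120/0.9 = 133.3, and the article states 133. The stated size reproduces for the unadjusted test.

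**2. Cost of simple randomisation in arm sizes.** With 240 analysed, 95% of allocations fall between 105/135 and 135/105. Power at those limits is 79% to 80%, so almost nothing is lost.

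**3. Link between number and endpoint.** In the limiting case of independent lesions, each clearing with probability 0.80 (an assumption), complete clearance is 0.8^k: 80%, 64%, 51% and 33% for k = 1, 2, 3 and 5. With perfect within-patient correlation there is no gradient.

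**4. Power with adjustment for number.** The article gives neither the distribution of counts nor their prognostic strength, so both were assumed and varied.

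- Counts of 1, 2, 3, 4, 6 and 10 had probabilities 0.45, 0.20, 0.12, 0.08, 0.08, 0.07 (wide) or 0.70, 0.15, 0.07, 0.04, 0.03, 0.01 (narrow).
- Lesion clearance followed a beta-binomial model with within-patient correlation ρ.
- Marginal cure was held at 70% versus 85%, with 240 analysed and simple randomisation.
- The chi-squared test was compared with a likelihood-ratio test from a logistic model on allocation and log2(number). Each setting used 4,000 runs, giving a Monte Carlo standard error of √(0.8·0.2/4000) ≈ 0.6 points on each power.

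| ρ | Wide: unadjusted → adjusted | Narrow: unadjusted → adjusted |
|---|---|---|
| 0 | 0.801 → 0.850 | 0.808 → 0.857 |
| 0.25 | 0.798 → 0.826 | 0.802 → 0.822 |
| 0.5 | 0.802 → 0.817 | 0.805 → 0.815 |
| 0.75 | 0.801 → 0.802 | 0.802 → 0.808 |
| 1 | 0.798 → 0.804 | 0.796 → 0.799 |

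The gain is about 5 points with independent lesions, 1 to 3 points at moderate correlation, and under 1 point from ρ = 0.75 upwards.

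A second simulation set the odds ratio of cure per doubling of number directly, again with an assumed spread of counts. Power was unchanged at about 0.80 for odds ratios of 1.0 and 0.8. It rose from 0.81 to 0.83 at 0.65, from 0.80 to 0.84 at 0.5, and from 0.80 to 0.89 at 0.35. The last is a very strong covariate and is best read as an outer bound. Under the null, both tests rejected in 4.6% to 5.9% of runs.

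**5. Chance imbalance.** For a binary factor of prevalence f at 120 per arm, the SD of the difference in prevalence is √(2f(1−f)/120).

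- f = 0.30: SD 0.059, P(|difference| ≥ 0.10) = 0.091.
- f = 0.50: SD 0.065, P(|difference| ≥ 0.10) = 0.121.

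If the factor lowers cure by 10 to 30 points (assumed), a 10-point imbalance shifts the raw difference by 0.10 × 10 to 0.10 × 30, or 1 to 3 points. The standard error of the raw difference is √(0.21/120 + 0.1275/120) = 5.3 points, so the shift is about 0.2 to 0.6 standard errors.

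**The case against.** The strongest reply is that nothing planned is lost. The trial was sized for exactly this test, and the size reproduces. Type I error is close to 5%, and design and test agree. A reader might infer that the chi-squared test is invalid, that planned power is being lost, or that the test is defenceless against imbalance. The article supports none of these. Chance imbalance after simple randomisation is part of the sampling variation that the p-value already allows for. Nor are type and previous treatment left uncovered, because the adjusted repeat includes both.

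Three further replies have weight:

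- The gain depends on unknown quantities. Lesions in one patient share the same treatment, adherence and healing, so independence is the extreme case and the gain may be negligible.
- Adjustment is not wholly free. At the design rates only 0.30 × 120 + 0.15 × 120 = 36 + 18 = 54 non-cures are expected, which limits the number of covariates. Previous treatment and duration are self-reported by questionnaire and may be missing.
- The trial is open and has recruited since October 2006, so replacing a declared primary test carries some cost in credibility.

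All of this lowers the weight of the point, but the omission remains. It cannot be put down to detail left for an analysis plan, because the article names the covariates of the repeat and leaves only those of the Cox model open.

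**Conclusion.** The point holds as one of efficiency and robustness, and is not an error in the primary test. An already collected covariate that bears directly on whether every verruca can clear is used nowhere in the stated 12-week analyses.

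Under the lesion-correlation model the benefit of using it is about 0 to 5 points of power, from about 80% to between 80% and 85%. Protection against chance imbalance is also modest: roughly one trial in ten would show a 10-point imbalance in a given binary factor, worth about 1 to 3 points on a 15-point target difference. The power range rests on assumed counts and correlations. The shift rests on the assumed effect of the factor on cure. The facts about what the plan includes and omits are certain; the size of the gain is not.

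**What to change.** Before any unblinded outcome data are seen, prespecify a logistic model for 12-week clearance on allocation, age, previous treatment, type and baseline number of verrucae (for example on a log scale). Report a standardised risk difference with 95% CI. Preferably this becomes the primary analysis, with the chi-squared test kept as supportive. At minimum, add number to the adjusted repeat already planned. The count must be the one before treatment starts; the article does not say when it is recorded, so this should be stated.

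**Cost:** free to cheap. It needs wording in the analysis plan and a dated amendment, with no new patients or visits. Three points need care:

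- The model's odds ratio is conditional on the covariates, so the standardised risk difference should stand beside it.
- A simple rule for missing covariates must be written, so that no patient is dropped from the intention-to-treat comparison.
- With about 54 non-cures expected, the covariate list should stay short. Duration is optional.

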The primary objective of the EVERT trial is to compare the clinical effectiveness of cryotherapy versus salicylic acid for the treatment of verrucae. Secondary objectives are to compare the cost-effectiveness of cryotherapy versus salicylic acid, and to investigate time to clearance of verrucae, recurrence/clearance of verrucae at six months, patient satisfaction with treatment, pain associated with treatment, and use of painkillers for the two treatments.

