#### Secondary outcomes

Secondary outcomes are time to clearance of verrucae, clearance of verrucae at six months, pain intensity of the first treatment (on a scale of 0 to 10, where 0 is no pain and 10 is the worst pain imaginable), use of painkillers due to verruca treatment (number of days painkillers taken), and patient satisfaction with the treatment (on a 5 point scale, from 'very unhappy' to 'very happy'). All secondary outcome measures are self-reported by the patient and assessed by questionnaire (either paper or web-based according to the patient's preference), which patients are requested to complete at baseline, just after the first treatment and at 1, 3, 12 and 24 weeks. Patients are supplied with a form to return to York Trials Unit when their verruca has gone.

For the economic evaluation, data on the number of visits to healthcare professionals in relation to verruca treatment (trial investigator and any other) and cost of other verruca treatments purchased by the patient are collected in the 12 week questionnaire completed by the patient and from clinic records of attendance.

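### Pain, painkiller days and satisfaction are secondary outcomes under the 0.01 rule, but the plan only describes them and gives no between-arm estimate

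*Protocol article*

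**What the plan says.** The closing paragraph of the Background lists the secondary objectives. Among the things to be investigated are "patient satisfaction with treatment, pain associated with treatment, and use of painkillers for the two treatments".

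The Secondary outcomes section turns these into measured outcomes. Besides time to clearance and clearance at six months, it names a 0 to 10 rating of pain at the first treatment, "use of painkillers due to verruca treatment (number of days painkillers taken"), and satisfaction on a 5-point scale.

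The Statistical analysis section then does two things:

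- It fixes a level: "For the secondary outcomes stricter statistical levels of significance will be adopted (i.e. p = 0.01) to reduce the chance of type I error". No secondary outcome is exempted. The text that follows gives Cox regression for time to clearance and, for six-month clearance, the same analysis as the primary outcome.
- In a later paragraph it deals with the remaining three. One sentence begins "Data on side effects and pain intensity during and after treatment, use of painkillers, reasons for seeking treatment for the verruca", goes on to treatment details, and closes with "patient satisfaction with treatment and number of verrucae, will be summarised and descriptive summary statistics provided". It does not mention treatment group. The next two sentences, on discontinuations and adverse reactions, do.

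**The concern.** A significance level only has meaning where a comparison is planned. Three of the five named secondary outcomes fall under the 0.01 level, yet the only analysis stated for them is a summary, in the same list as items that are not outcomes at all, such as reasons for seeking treatment and number of verrucae.

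This is more than a detail left for an unseen analysis plan. The article does not leave the analysis of these outcomes open; it states one, and that analysis does not fit its own rule.

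The outcomes affected matter to the trial's purpose. The Background points to pain and blistering with cryotherapy alongside a lack of evidence that it works better than topical treatment. If clearance turns out similar in the two arms, differences in pain, painkiller use and satisfaction will weigh in the choice between treatments. With no planned contrast, readers are left to compare columns by eye, and any test added later would be unplanned, which is what a stricter level is meant to guard against.

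**Working it through.** **1. Outcomes set against analyses**

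| Secondary outcome (Secondary outcomes section) | Under the 0.01 level? | Between-arm analysis stated? |
|---|---|---|
| Time to clearance | Yes | Cox regression |
| Clearance at six months | Yes | As for the primary outcome (chi-squared) |
| Pain at first treatment, 0 to 10 | Yes | None; descriptive |
| Days of painkiller use | Yes | None; descriptive |
| Satisfaction, 5-point | Yes | None; descriptive |

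Five are named, two are compared and three are described.

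**2. The plan's own sample size**

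Inputs from the Sample size section: 70% v 85%, two-sided 5%, 80% power, 10% drop-out; stated result 120 per group, 133 after drop-out.

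- Pooled variance: n = [1.96 × √(2 × 0.775 × 0.225) + 0.842 × √(0.7 × 0.3 + 0.85 × 0.15)]² / 0.15² ≈ 120.5, so 121.
- Unpooled variance: n = (1.96 + 0.842)² × (0.21 + 0.1275) / 0.0225 ≈ 117.7, so 118.
- Power at 120 per group: 79.8%.
- Drop-out: 120 / 0.9 = 133.3.

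The stated figures are reproduced closely enough. The point does not depend on them; they only supply the number per arm for the next step.

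**3. Is a between-arm estimate worth having at this size?**

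The article gives no SD for the pain scale, so a range of 2 to 3 points is assumed.

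- 99% half-width = 2.576 × SD × √(2/120) = 0.333 × SD.
- SD 2: 0.67 points. SD 2.5: 0.83 points. SD 3: 1.00 points.
- Difference detectable with 80% power at 0.01 = (2.576 + 0.842) × SD × √(2/120) = 0.441 × SD, that is 0.88 points (SD 2) to 1.32 points (SD 3).

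If all 133 per arm gave a pain rating, the half-width would be 0.316 × SD, or 0.63 to 0.95 points.

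**4. Cost in multiplicity**

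Treating the tests as independent, the chance of at least one false positive is 1 − 0.99² = 2.0% for the two outcomes now tested and 1 − 0.99⁵ = 4.9% if all five were tested at 0.01.

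**The case against.** The best defence is that description was a deliberate choice. The Background speaks of comparing effectiveness and cost-effectiveness but only of investigating pain, painkiller use and satisfaction, and keeping tests to the clearance outcomes limits multiplicity. This has some force: a descriptive analysis does not flatly contradict the wording of the objective. It is not decisive, because time to clearance is also listed under investigation and does get a formal comparison, and because the 0.01 level is stated for the secondary outcomes without restriction.

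A second defence is that the information is not lost. If means, SDs and numbers are shown by arm, as is likely though not stated, a reader can derive a crude pain difference and its interval. That stands, so the gap is a missing planned contrast and not missing data.

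Three stronger readings are tempting and should be resisted:

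- *That the 0.01 rule has nothing to apply to.* It applies to time to clearance and six-month clearance. It lacks a test only for the other three.
- *That the trial could draw no conclusion on tolerability, or that tolerability alone would settle the choice.* By-arm summaries would still inform, discontinuations and suspected adverse reactions are to be shown by group, and the Economic analysis section plans a formal cost-effectiveness comparison.
- *That rating pain at the first treatment treats the arms unequally, because it is one of at most four cryotherapy sessions (25% or more) but one of up to 8 × 7 = 56 daily acid applications (about 2%).* Those shares count applications; they show neither the size nor the direction of any bias in pain. Later tolerability is picked up by painkiller days, satisfaction, adverse events and discontinuations, and the Statistical analysis wording itself extends to pain during and after treatment. A repeated pain item would also come late, since recruitment runs from October 2006 to about December 2009, and would be missing for many patients.

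**Conclusion.** The point holds in a limited form. Three of the five named secondary outcomes come under the 0.01 level but have only descriptive summaries planned, not stated to be by treatment group, so the tolerability objectives get no planned between-arm estimate. The primary result, the sample size and the economic outcome are unaffected.

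The half-width of about 0.7 to 1.0 points on the 0 to 10 pain scale shows that a useful estimate is feasible; it does not measure an error in the plan. It rests on about 120 evaluable patients per arm and on the assumed SD. No comparable figure can be given for painkiller days or satisfaction from what the article states. The inconsistency is worth removing before the analysis.

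**What to change.** Take first-treatment pain, painkiller days and satisfaction out of the descriptive list in the Statistical analysis section. For each, pre-specify a between-arm difference by randomised group with a 99% confidence interval, to match the 0.01 level, using a method suited to the scale: for example a mean difference for pain, a count model or rank-based comparison for painkiller days, and an ordinal model for satisfaction.

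If the intention really is to describe these outcomes, the least that is needed is to say so, state that the summaries are by treatment group, and limit the 0.01 level to the two tested outcomes. That removes the inconsistency but still leaves the tolerability objectives without an estimate.

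The data are already being collected, so no new questionnaire item or visit is required. The cost is plan wording, a little more analysis, and three more comparisons at the 0.01 level.

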## Background

Verrucae or plantar warts are a common, infectious and sometimes painful problem. Although most verrucae will spontaneously disappear without treatment many patients seek treatment to remove a verruca due to it being painful or because they are being prevented from doing sports and other activities of daily living. Two common treatments for verrucae are cryotherapy using liquid nitrogen which involves freezing the tissues at below -60C or application of a salicylic acid paste which macerates the skin. Using incidence figures from the 4th National Morbidity Survey [1], an economic decision model assessing the effectiveness and cost-effectiveness of salicylic acid and cryotherapy has estimated that almost 2 million people in England and Wales see their General Practitioner (GP) per year about cutaneous warts at a cost of at least £40 million per annum [2].

A systematic review conducted by the Cochrane Skin Group assessed the effects of different local treatments of cutaneous, non-genital warts in healthy people [3]. This review highlighted the uncertainty with respect to the optimal treatment of verrucae. There was, however, some evidence from six trials to suggest that treatment with salicylic acid was more effective than placebo/no treatment, odds ratio 3.91 (95% confidence interval (CI) 2.40 to 6.36). Many patients experience unpleasant side effects such as pain and blistering during cryotherapy treatment, yet the same review found no evidence to suggest that it is more effective than treatment with topical agents such as salicylic acid. Only two trials were identified which compared salicylic acid and/or lactic acid with cryotherapy, and they found no difference in the efficacy between the treatments (odds ratio 1.15, 95% CI 0.72 to 1.82). However, both trials were reported as low quality, due to unclear allocation concealment, inadequate blinding procedures, small sample sizes and inappropriate follow-up and analysis. There is a need, therefore, for a high quality randomised controlled trial with a cost-effectiveness analysis to ascertain which is the better approach for the treatment of verrucae.

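### The only adverse event incidence planned by treatment group is limited to suspected treatment reactions, in an open trial that does not say who makes that judgement

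*Protocol article*

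**What the plan says.** Under Further data collected, the protocol article sets a broad scope for collection: "Data on adverse events, self-reported by the patient (verbally and/or by questionnaire) or elicited by the healthcare professional", the latter by questioning at each visit. Nothing there restricts the data to events thought to be caused by treatment.

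Under Statistical analysis, the one sentence that plans an adverse event incidence by arm is narrower: "The incidence of all suspected adverse treatment reactions will be summarised by treatment group". No sentence plans the incidence of all adverse events by arm.

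The same paragraph plans two other relevant summaries. One is descriptive and begins "Data on side effects and pain intensity during and after treatment, use of painkillers"; it does not state a split by group. The other is "The number of patients discontinuing treatment prematurely for any reason will be summarised by treatment group and by reasons for discontinuation".

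On blinding, the Design section states "This is an open, pragmatic, two-arm, multicentre, randomised controlled trial", and Statistical analysis gives a reason for its preference subgroup that begins "As patients and healthcare professionals are not blinded to treatment". Blinding is stated for the 12-week clinical assessment of clearance and for the conduct of the analyses. It is not stated for any judgement about the cause of an adverse event.

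**The concern.** Whether an event is a suspected reaction is decided after randomisation. If that decision is made with knowledge of the arm, the same event can be counted in one arm and left out in the other. The tabulated incidence then mixes what happened to patients with what someone believed about the cause.

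Two features of this trial make unequal attribution plausible. The Background section already records an expectation about one arm: "Many patients experience unpleasant side effects such as pain and blistering during cryotherapy treatment". The arms also differ in planned contact. Under Interventions, both arms have appointments at 2 and 12 weeks, but cryotherapy patients may attend up to two further treatment visits, whereas acid patients treat themselves at home.

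What is at stake is the between-arm comparison of harms. The abstract lists side effects, as part of patient acceptability, among the things the trial is to compare. A harm that nobody suspected of being treatment-related, and that did not stop treatment, might not appear in the one adverse event incidence planned by arm. The primary outcome and its analysis are not affected.

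**Working it through.** The protocol gives no expected safety rate or safety figure, so there is nothing of its own to reproduce. The check has two parts.

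**1. The text, step by step**

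- Scope of collection: all adverse events (Further data collected).
- Scope of the by-arm incidence: suspected reactions only (Statistical analysis).
- Who applies the label: not stated in the article.
- Whether that person is blinded: not stated. The people who report and elicit events are unblinded. Blinding the analyst does not help, because the label is presumably already in the data by then. The Data Monitoring and Ethics Committee reviews safety data (Study organisation), but no role in adjudicating cause is given.
- Summaries outside the filter: the total of discontinuations, given by group, and pain intensity of the first treatment, a patient score from 0 to 10 (Secondary outcomes).
- Summaries that do not fully escape it: side effects, because the term itself implies a cause, and painkiller use, because it is recorded as due to verruca treatment.

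**2. What the filter could do to the table**

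Inputs: 133 patients per arm (Sample size). All other values are assumptions chosen for illustration; none is in the documents.

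Let *r* be the true proportion of patients with an event, equal in both arms, and *a*₁ and *a*₂ the share of those patients whose event is labelled suspected in each arm. Then:

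- displayed incidence = *r* × *a*₁ and *r* × *a*₂
- displayed ratio = *a*₁ / *a*₂, whatever the value of *r*
- displayed difference = *r* × (*a*₁ − *a*₂)

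| True incidence, both arms | Attribution | Displayed incidence | Patients of 133 | Difference (points) | Ratio |
|---|---|---|---|---|---|
| 10% | 80% v 80% | 8% v 8% | 10.6 v 10.6 | 0 | 1.0 |
| 10% | 80% v 60% | 8% v 6% | 10.6 v 8.0 | 2 | 1.33 |
| 10% | 80% v 40% | 8% v 4% | 10.6 v 5.3 | 4 | 2.0 |
| 20% | 80% v 80% | 16% v 16% | 21.3 v 21.3 | 0 | 1.0 |
| 20% | 80% v 60% | 16% v 12% | 21.3 v 16.0 | 4 | 1.33 |
| 20% | 80% v 40% | 16% v 8% | 21.3 v 10.6 | 8 | 2.0 |
| 30% | 80% v 80% | 24% v 24% | 31.9 v 31.9 | 0 | 1.0 |
| 30% | 80% v 60% | 24% v 18% | 31.9 v 23.9 | 6 | 1.33 |
| 30% | 80% v 40% | 24% v 12% | 31.9 v 16.0 | 12 | 2.0 |

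The filter can also hide a real difference. With true incidence of 10% in one arm and 20% in the other, and attribution of 80% and 40% respectively, the displayed figures are 0.10 × 0.80 = 8% and 0.20 × 0.40 = 8%. A true ratio of 2.0 would be shown as 1.0.

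The table of suspected reactions cannot reveal which of these situations applies. An all-event table beside it could, because dividing one by the other gives the attribution share in each arm.

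**The case against.** The strongest reply is that the article says what will be summarised, not that other adverse events will be left out. A journal article condenses the full plan, and the list of safety tables is commonly kept there. A reader might infer that unattributed harms will never be shown by arm; the document does not support that. An all-event table may exist in a document that is not shown, and an unattributed harm that ended treatment would be counted among discontinuations. The point survives in a narrower form: for by-arm incidence, the text does more than stay silent. It names a particular set of events, and that set is the filtered one.

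A reader might also infer that an unblinded judgement decides the whole safety comparison. It does not. Discontinuations and pain intensity are summarised without passing through the filter, and pain is one of the two cryotherapy harms that the Background names. This limits the point to the planned adverse event incidence.

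Nor do the documents say that the treating professional labels events. That the labelling is unblinded is a reasonable inference from the open design, not protocol content. It would also be wrong to picture acid patients as out of contact after the first visit. They have a safety check at 2 weeks and a visit at 12 weeks, and both arms receive questionnaires at 1, 3, 12 and 24 weeks. The monitoring committee's review of safety data carries no stated limit to suspected reactions.

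Finally, an all-event table is not free of bias here. Events are elicited at visits, the arms may differ in their number of visits, and reporting is open-label. An event missed at collection stays missed. This stands, and it limits what the fix can achieve.

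**Conclusion.** The concern holds in a limited form. Adverse events are collected irrespective of cause, but the only adverse event incidence that the article plans by treatment group is that of suspected reactions. In an open trial with no stated assessor and no stated blinding of the judgement, that is an analysis choice exposed to unequal attribution between arms.

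Size and direction are unknown. Equal attribution gives no distortion. Assumed attribution of 80% v 60% or 80% v 40% gives spurious ratios of 1.33 or 2.0 when the true incidence is equal. These figures show how the mechanism works and are not estimates for this trial.

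The conclusion rests on two assumptions: that the label is applied with knowledge of the arm, which is probable but not stated, and that no all-event table is planned in a document not shown. It concerns the by-arm adverse event incidence alone.

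**What to change.** In the Statistical analysis section, or in the analysis plan, make the main by-arm safety table one of all adverse events regardless of suspected cause. Give the number and percentage of patients with at least one event, then the breakdown by type, with local foot events shown separately. Keep suspected reactions as a secondary table, and state beside it who attributes cause and whether that person knows the allocation.

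The cost is one extra table and a sentence or two. The events are already collected, so data collection, sample size and the primary analysis do not change. The downside is dilution by unrelated background events, which the separate display of local foot events partly offsets.

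The report should also state that the new table removes the attribution layer only, and that unequal numbers of visits and open-label reporting remain as limitations of the comparison.
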